# ANNEX III

ANNEX V. **Case report form and questionnaires**

**Mucosal immunity study in Moradabad**

**QUESTIONNAIRE – ENROLLMENT**

**Date ______ / _______ / ________**

# Identification data

# Child’s name:

# DOB: ____ \ _____ \ _____ Age: ______ years ______ months Sex F / M

Name of father:________________________________________________________________________

Address: Landmark:

# Village Block: CMC area

**Eligibility criteria**

- Child’s residence < 30 km from study site Yes / No
- Child’s age: 6-11 months, 61- 72 months or 120 – 131 months? Yes / No
- Child and family planning to travel / move in the next 2 months? Yes / No
- Diagnosis or suspicion of immunodeficiency in the child or family member? Yes / No
- Child has known coagulation disorders that contraindicate venipuncture? Yes / No
- Child has history of severe allergic reaction to a medication or to OPV? Yes / No
- Has the child had diarrhea in the last 1-2 days (3 or more liquid stools per day)? Yes / No
- Does the child have any acute infection or other acute condition now? Yes / No

If yes, specify _____________________________________

Temp: _________

**Based upon the above criteria is this child a candidate for the study? Yes / No**

***If child has any of the previous criteria that contraindicates participation, STOP THE QUESTIONNAIRE;*** *provide medical advice and oral medication if required, and say farewell.*

***If the child fulfills the enrollment criteria, EXPLAIN THE STUDY to the parents.***

**Parent/guardian’s response**

Accept participation Reject participation

***If parents REJECT to participate or NOT AVAILABLE*** *for the study duration, STOP and say farewell.*

***If parents ACCEPT to participate*** *arrange transportation to study site.*

**Name and signature of investigator:** ___________________________________________________

**Mucosal immunity study in Moradabad**

**Day 0 Procedures**

**Date _____ / _______ / _______ Child ID number:**

# Explanation and review of consent form

# Informed consent obtained? Yes / No

# Name and signature of person obtaining consent: ______________________________

# Epidemiology data

# DOB: ____ \ _____ \ _____ Age: ______ years ______ months Sex: F / M

Religion: H / M / O Father’s occupation:

Father’s education (encircle): Illiterate / Primary / Middle / Tenth / Twelfth / Graduate

Number of people in household (parents & siblings only): ­­

Number of children <5 years in household (study subject):

# Clinical exam

# Height: _________ cms Weight: ___________ kgs Temp: _____ F

**Sample collection**:

Blood collected? Yes / No Quantity sufficient (≥1ml)? Yes / No

If blood not collected, explain reasons:

Saliva sample collected? Yes / No

If saliva not collected, explain reasons:

Stool sample collected? Yes / No Date of collection ___ / ____ / ___

If stool not collected, explain reasons: _______________________________________________

Name and signature of responsible for sample collection:

**Vaccine administration**:

Type of vaccine administered: Intramuscular (IPV) Oral (bOPV) No vaccine

Lot and Batch number: Exp date: ___ / ___/ ___ Time of administration: ___ : ___

If intramuscular IPV, site of administration: Right arm Left arm

Observation for 30 minutes after vaccine administration:

Temp ________ Any symptoms: Yes / No.

If yes, describe symptoms: _______________________________________________________

If intramuscular IPV: Swelling: None <1 cm 1-3 cm > 3 cm

Redness: None <1 cm 1-3 cm > 3 cm

Name and signature of vaccinator _________________________________________

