This design will provide the first data on mucosal immunity in children living in high risk areas in India. This trial will also assess which polio vaccines are more efficient in boosting mucosal immunity, which would provide an effective barrier to subsequent excretion and community spread of poliovirus. The data from this trial will likely have programmatic implications, especially in determining whether the current age range for SIAs (children aged <5 years) should be re-evaluated. Additionally, the trial will compare different markers of mucosal immunity such as measurement of secretory immunoglobulin A (sIgA) levels in gingival fluid or stools and ELISPOT test, with the gold standard test, which is the measurement of vaccine virus shedding after a challenge with a known dose of OPV. Identifying new surrogate markers of mucosal immunity is important because the challenge test requires high workload and resources, and its use in the post-eradication era may not be possible.

Summary of known and potential risks:

The main serious adverse event associated with oral poliovirus vaccines, including bOPV, is VAPP. Outside the first few months of life, the risk of VAPP is small; approximately 1 case per 1 million doses of tOPV administrated [9, 10], and associated primarily with type 3 and type 2 components of the tOPV. Since bOPV does not contain the Sabin type 2 component, we can assume that the already very low risk of VAPP is even lower following bOPV administration. However, the exact risk of VAPP following bOPV is currently unknown. The only experience with bOPV is available from Estonia, Lithuania and Hungary from 1959-1960. Here the experience is mixed, while Estonia and Lithuania reported no VAPP [10-14], Hungary reported an increase in VAPP [15-17]. The other potentially serious adverse events are anaphylactic reactions. Since OPV and IPV vaccines contain trace amounts of antibiotics, anaphylactic reactions to these antibiotics are possible, but appear to be exceedingly rare. IPV is one of the safest available vaccines, and no systemic serious adverse events are linked to this product. As with all injectable vaccines, minor local adverse events at the injection site are relative frequent.

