# Trial Objectives and Purpose

## Mucosal immunity:

- To compare baseline mucosal immunity (through different methods) among three age groups with several degrees of protection acquired through immunization:
  - Infants 6-11 months of age will have received a few OPV doses
  - Children 5-6 years of age will have received multiple OPV doses in campaigns and are expected to have the highest levels of mucosal and humoral immunity
  - Children 10-11 years of age will not have received booster OPV doses for > 5 years. They are expected to have high antibody titers but may have waned mucosal immunity.
- To determine whether one dose of bOPV or IPV significantly reduces excretion of poliovirus types 1 and 3, respectively, following a challenge dose with bOPV, compared to an unvaccinated control arm.
- To determine whether one dose of bOPV or IPV significantly increases sIgA in crevicular fluids and stool samples, and to examine whether the increase in specific SIgA in these specimens is correlated to a reduction in excretion of Sabin poliovirus types 1 and 3 following the challenge with bOPV. This will allow evaluating the use of sIgA as a surrogate test for assessment of mucosal immunity.
- To determine the robustness of the mucosal immune response by study arm and age group, by measuring poliovirus antibody-secreting cells in an ELISPOT-spot assay 7 days after the administration of the study vaccine.

Humoral immunity:

- To determine whether one dose of bOPV or IPV will significantly increase seroprevalence and booster antibody titers compared to unvaccinated children.
- To assess whether one dose of IPV will significantly increase seroprevalence and antibody titers compared to a single dose of bOPV.
- To examine the correlations between antibody titers in blood and shedding of poliovirus after a challenge dose, for each vaccine study arm and age group.
- To examine the correlation between levels of IgA in serum and levels of secretory IgA in crevicular fluids and stool samples, before and after the booster vaccine dose, to gain further understanding on the mechanisms of mucosal immunity against poliovirus.
- To analyze correlations between levels of secretory IgA in crevicular fluids and stools and the ELISPOT test results, to better understand mucosal immunity against poliovirus.

Safety:

- To assess adverse events following vaccine administration.

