# Trial Design

Local community mobilization coordinators (CMCs) working with the Global Polio Eradication Initiative (GPEI) will identify families with children in the target age-group (i.e. 6-11 months, 5-6-years, and 10-11-years). Surveillance Medical Officers (SMOs) will visit households of potential candidate families, explain the study to the parents or guardians, and facilitate transportation to one of the study sites for those interested to participate. Approximately 10 study sites will be chosen in areas identified as high-risk for poliovirus transmission.

At the study site, a physician will conduct a short interview and physical examination. After obtaining informed consent from the parents (and assent from children of age 10-11 years), the study participant will be assigned a study number and allocated to a study arm. For this, the parent or child will select a closed envelope that includes the study arm from a basket. Then a baseline blood sample collected by venipuncture, oral (crevicular) fluid, and stool samples will be collected before vaccine administration.

Note: crevicular fluid will not be collected in the 6-11 month age group because of the absence of teeth.

In a subset of children 10-11 years of age (~175-200 children) a second blood sample will be collected at 7 days by venipuncture for the ELISPOT test.

In all children, at 28 days, another blood sample by venipuncture, another oral (crevicular) fluid sample and a stool sample will be collected before the subjects receives the challenge vaccine (bOPV). Thereafter, at days 3, 7 and 14 stool samples will be collected. And finally, at day 56, another serum sample and oral fluid sample will be collected. At this time, having fulfilled the study requirements, the children will exit the study.

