**Mucosal immunity study in Moradabad**

**Day 7 Procedures *(Only a subset of children)***

**Date _____ / _______ / _______ Child ID number:**

# Parent/Guardian agrees to attend the second study visit? Yes / No

# If no, specify reasons: _________________________________________________________________ ____________________________________________________________________________________

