# Clinical exam

Child healthy? Yes / No *(If No, fill the adverse event form, and provide advice/referral)*

Since the last visit, - Has the child required hospitalization? Yes / No

- Has the child required a visit to a physician/clinic for health problems? Yes / No

If yes to previous hospitalization / physician visit, has the adverse event form been completed? Yes / No

Name and signature of investigator/physician:

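### The safety objective covers adverse events in general, but the forms cannot record a minor event that starts after the 30-minute observation, needs no care and resolves before the next visit

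*Protocol*

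**What the plan says.** - **Objective** (Trial Objectives and Purpose, Safety): "To assess adverse events following vaccine administration". It is not limited to serious or medically attended events.
- **Expected events** (Summary of known and potential risks): with injectable vaccines, "minor local adverse events at the injection site are relative frequent". No rate or time of onset is given.
- **Day 0 form** (Annex V, Vaccine administration): under "Observation for 30 minutes after vaccine administration", temperature, any symptoms and, for IPV, local signs graded by size, as in "If intramuscular IPV: Swelling: None <1 cm 1-3 cm > 3 cm" and the matching item for redness.
- **Day 7, 28 and 56 forms** (Annex V, Clinical exam): "Child healthy? Yes / No", a question on hospitalization since the last visit, and "Has the child required a visit to a physician/clinic for health problems? Yes / No". A child who is not healthy, or a positive answer on care, calls for the adverse event form.
- **Who is seen on day 7**: the form is headed "Only a subset of children". Trial Design limits this visit to about 175 to 200 children aged 10-11 years, for the ELISPOT test.
- **Assessment of Safety**: parents are told to make contact if the child needs medical care and are encouraged to use the study institution. The questionnaire is to cover each visit and, where applicable, the period before it.

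**The concern.** The objective and the forms do not match. The protocol names minor local reactions as the events to expect after an injected vaccine, but looks for them once, within half an hour of the injection. After that, the only look-back questions concern hospitalization and physician or clinic visits. A child whose arm swelled that evening, or who had a fever the next day, and who was well again without seeing anyone, answers every later question in a way that opens no adverse event form.

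What is at stake is what the trial may conclude about safety. If the objective stays general, a small number of local or minor systemic events could be read as a finding about the vaccines when it partly reflects what was asked. The gap lies in data collection, so no analysis plan could recover the missing information.

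**Working it through.** The protocol states no figure on this point, so there is none to reproduce. The check has three steps.

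**1. Go through every form for a question that would catch the event.** Take an event that starts after 30 minutes, is not medically attended and has resolved by the next visit.

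| Form | Safety content | Catches it? |
|---|---|---|
| Day 0 | Temperature, symptoms, IPV swelling and redness within 30 minutes | No, too early |
| Day 7 (subset) | Healthy now; hospitalization; physician or clinic visit | No |
| Day 28 | Same three items before the challenge dose; problems within 15 minutes after it | No |
| Days 31, 35, 42 (household) | Stool collection only | No |
| Day 56 | Same three items as day 7 | No |
| Adverse event form | Free text, completed when another form or a report calls for it | Only if triggered |

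The statement under Assessment of Safety that the questionnaire covers the preceding period does not close the gap, because the only look-back items printed on the questionnaire are hospitalization and physician or clinic visits.

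**2. Count the children without a scheduled contact between 30 minutes and day 28.** Inputs: 990 enrolled, 110 per age group and arm (Annex I); day 7 subset of 175 to 200 (Trial Design).

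- 990 − 200 = 790, and 790/990 = 79.8%.
- 990 − 175 = 815, and 815/990 = 82.3%.
- IPV arm: 3 × 110 = 330. None of the 330 has an injection-site item after the 30-minute block. If the subset splits evenly over the three arms (an assumption), 330 − 200/3 = 263 to 330 − 175/3 = 272 IPV recipients have no scheduled contact before day 28.

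**3. Ask whether the size of the under-count can be derived.** Let f be the share of reactions visible within 30 minutes, and s the share of the rest that still reach a form (present at a visit, medically attended or reported spontaneously). Then

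recorded rate / true rate = f + (1 − f) × s.

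This ratio is below 1 unless f = 1 or s = 1, which fixes the direction. The documents give neither f nor s. Under assumed ranges:

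- f = 0.05, s = 0: 0.05 + 0.95 × 0 = 0.05.
- f = 0.50, s = 0.30: 0.50 + 0.50 × 0.30 = 0.65.

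A span of 5% to 65% of the true rate, resting wholly on assumed inputs, shows that the documents do not determine the size.

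**The case against.** The strongest reply is that the protocol defines its safety parameters more narrowly than its objective. Specification of the safety parameters is built on a child who requires medical care and on serious illness leading to a physician's visit or hospitalization, and the visit forms carry out exactly that. Both vaccines are licensed in India, the protocol describes the safety profile of IPV as well characterized, and the trial is about mucosal immunity. Collecting immediate, medically attended and serious events is a defensible choice. This stands, and it is why limiting the objective is an adequate alternative fix. It does not remove the mismatch, because the objective itself carries no such limit.

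Three stronger readings are tempting, and the documents do not support them:

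- **That the trial will report a falsely low IPV reaction rate.** The protocol specifies no local-reaction endpoint, safety hypothesis or safety analysis. Results labelled as 30-minute observations and medically attended events would be accurate. They would mislead only if presented as a full account of adverse events.
- **That nothing is captured after 30 minutes.** A reaction still present at a visit, one that led to care, or one that a parent reports can reach the adverse event form. Serious events have their own tick boxes and reporting route.
- **That age-group comparisons of adverse events are biased.** The day 7 and day 28 forms both look back to the last visit, so days 0 to 28 are covered for every child. Only the recall interval differs for the subset. No comparison of adverse events by age group is planned, and no material bias is shown.

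**Conclusion.** The point holds for minor local or systemic events that start after 30 minutes, need no care, resolve before the next visit and are not volunteered. Such events are asked about on no form, so they are under-counted. The structural size is firm: about 790 to 815 of 990 children have no scheduled contact from the 30-minute observation to day 28, assuming full enrolment and the stated subset size, and no IPV recipient has a later injection-site item. The share of events missed cannot be derived, because neither the reaction rate nor the time of onset is given. The primary endpoint is unaffected, and serious and medically attended events are captured. This is a cheap improvement worth making, not a failure of the trial's safety oversight.

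**What to change.** **Preferred.** Add one look-back item to the existing day 7 and day 28 forms, asked by interview: any fever, any redness, swelling or pain at the injection site (IPV recipients), or any other illness since vaccination, even if no care was sought. A positive answer triggers the adverse event form. The cost is one item on two forms, with no new visit. The downside is recall error of up to 28 days, in a trial where parents know the allocation, so reporting could differ by arm.

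**Alternative.** Limit the safety objective and its conclusions to serious events, medically attended events and immediate (30-minute) reactions, in line with Specification of the safety parameters and the day 0 form, and label all local-reaction results as 30-minute observations. This is a change of wording only. The trial would then make no statement on later minor reactions.

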**Mucosal immunity study in Moradabad**

**Day 7 Procedures *(Only a subset of children)***

**Date _____ / _______ / _______ Child ID number:**

# Parent/Guardian agrees to attend the second study visit? Yes / No

# If no, specify reasons: _________________________________________________________________ ____________________________________________________________________________________

# Name and signature of person doing interview:

*If parents agree to the second visit, arrange transportation to the study site*

# Clinical exam

Child healthy? Yes / No *(If No, fill the adverse event form, and provide advice/referral)*

Since the last visit, - Has the child required hospitalization? Yes / No

- Has the child required a visit to a physician/clinic for health problems? Yes / No

If yes to previous hospitalization / physician visit, has the adverse event form been completed? Yes / No

Name and signature of investigator/physician:

**Sample collection**:

Blood collected? Yes / No Quantity sufficient (≥ 3 ml)? Yes / No

If blood not collected, explain reasons:

Name and signature of responsible for sample collection:

**Mucosal immunity study in Moradabad**

**Day 28 Procedures**

**Date _____ / _______ / _______ Child ID number:**

# Parent/Guardian agrees to attend the second study visit? Yes / No

# If no, specify reasons: _______________________________________________________________________________

# Name and signature of person doing interview:

*If parents agree to the second visit, arrange transportation to the study site*

# Clinical exam

Child healthy? Yes / No *(If No, fill the adverse event form, and provide advice/referral)*

Since the last visit, - Has the child required hospitalization? Yes / No

- Has the child required a visit to a physician/clinic for health problems? Yes / No

If yes to previous hospitalization / physician visit, has the adverse event form been completed? Yes / No

Name and signature of investigator/physician:

**Sample collection**:

Blood collected? Yes / No Quantity sufficient (≥ 3 ml)? Yes / No

If blood not collected, explain reasons:

Oral fluid sample collected? Yes / No

If oral fluid not collected, explain reasons:

Stool sample collected? Yes / No Date of collection ___ / ____ / ___

Quantity sufficient (≥ 10 g)? Yes / No

If stool not collected, explain reasons: _____________________________________________

Name and signature of responsible for sample collection:

**Administration of bOPV challenge dose**:

Oral bOPV administered? Yes / No Time of administration: (hh:mm) ___ : ____

If bOPV not administered, explain reasons: _______________________________________

Any problems within 15 minutes of administration (e.g. spitting, vomiting)?: Yes / No

Name and signature of vaccinator:

**Mucosal immunity study in Moradabad**

**Day 56 Procedures**

**Date _____ / _______ / _______ Child ID number:**

# Parent/Guardian agrees to attend the third study visit? Yes / No

# If no, specify reasons: __________________________________________________________________

# Name and signature of person doing interview:

*If parents agree to the second visit, arrange transportation to the study site*

# Clinical exam

Child healthy? Yes / No *(If No, fill the adverse event form, and provide advice/referral)*

Since the last visit, - Has the child required hospitalization? Yes / No

- Has the child required a visit to a physician/clinic for health problems? Yes / No

If yes to previous hospitalization / physician visit, has the adverse event form been completed? Yes / No

Name and signature of investigator/physician:

**Sample collection**:

Blood collected? Yes / No Quantity sufficient (≥ 3 ml)? Yes / No

If blood not collected, explain reasons:

Oral fluid sample collected? Yes / No

If oral fluid not collected, explain reasons:

Name and signature of responsible for sample collection:

**Mucosal immunity study in Moradabad**

**Day 31- Household stool sample collection**

**Date of visit _____ / _______ / _______ Child ID number:**

**Sample collection**:

Stool sample collected? Yes / No

If sample not collected, explain reasons:

*(Note: contact supervisory SMO for action if family not available at home or sample not collected for other reason. A second visit may be required for stool collection).*

Date when sample was collected _______ / ______ / ______

Quantity sufficient ((≥10 g)? Yes / No

Cold chain maintained? Yes / No

Name and signature of person responsible for stool collection:

**Mucosal immunity study in Moradabad**

**Day 35- Household stool sample collection**

**Date of visit _____ / _______ / _______ Child ID number:**

**Sample collection**:

Stool sample collected? Yes / No

If sample not collected, explain reasons:

(Note: contact supervisory SMO for action if family not available at home or sample not collected for other reason. A second visit may be required for stool collection).

Date when sample was collected _______ / ______ / ______

Quantity sufficient (≥10 g)? Yes / No

Cold chain maintained? Yes / No

Name and signature of person responsible for stool collection:

